### Adverse event reporting

#### Adverse events (AEs)

Adverse events are defined as any undesirable experience occurring to a subject during the study, whether or not considered related to experimental intervention. All adverse events with a direct or possible link to the OPRAH trial (e.g. AEs occurring during intervention-related activities) reported spontaneously by the subject or observed by the investigator or his staff will be recorded.

#### Serious adverse events (SAE)

This study includes patients undergoing oncological lung or GI surgery. These types of surgery are associated with a certain risk of postoperative complications. Our intervention starts after hospital discharge; therefore, all complications during hospitalization will not be reported as SAE. We expect that our, low-risk, post-discharge intervention will not have any negative influence on the occurrence complications after discharge. Therefore, all complications after discharge which are unmistakably caused by the surgery and/or medical treatment will not be reported as SAE. When there are doubts about the relation between the intervention and the occurrence of an SAE, these SAEs will be discussed with the surgeons involved in this study per patient group. If, after discussion, there is still any doubt about the relation between the intervention and the occurrence of an SAE, the SAE will be reported.

The participating hospitals will report SAEs within 24 h to the sponsor. The sponsor will report the SAEs to the accredited medical ethical committee that approved the protocol, within 7 days of first knowledge for SAEs that result in death or are life threatening followed by a period of maximum of 8 days to complete the initial preliminary report. All other SAEs will be reported within a period of maximum 15 days after the sponsor has first knowledge of the serious adverse events.

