#### Intervention description and procedures

One week prior to planned surgery, patients receive the PAM and will receive access to and get instructions about the Atris app to get familiarized with the application. Patients are asked to wear the PAM 24 h a day in a strap around the ankle, from at least 5 days prior to surgery until 3 months after surgery. During hospitalization, the treating physiotherapist and dietician guide the patients in the use of the app during their standard consultations. As the day of hospital discharge approaches, the patient will be supported by the physiotherapists and dietician using the SDM process to set goals on active minutes and protein intake for after discharge. After discharge to home, patients are coached remotely (by telephone and chat) by a physiotherapist and dietician about physical activity and protein intake during 3 months after discharge. Through a chat function in the app, patients can ask questions to the physiotherapist or dietician, the physiotherapist and dietician can also send information through the chat. The ultimate goal for physical activity is to return to pre-surgery level of physical activity. The ultimate goal for protein intake is to achieve the personal daily requirements. If the recovery stagnates and goals are not achieved, the physiotherapist or dietician will contact the patient to identify barriers in their recovery. The sub-goals and the degree of coaching will be tailored using a SDM process to the personal needs and preferences of the patient. To support patients’ self-management, MI techniques will be applied during the coaching sessions with the physiotherapist and dietician by telephone and chat [32].

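### The adverse event outcome counts only events linked to the trial, a filter that acts unequally by arm, and its in-hospital exemption assumes a start of intervention that the protocol contradicts

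*Protocol article*

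**What the plan says.** The protocol article's section on adverse events opens with a broad definition: "Adverse events are defined as any undesirable experience occurring to a subject during the study, whether or not considered related to experimental intervention". The next sentence sets a narrower rule for what is written down: "All adverse events with a direct or possible link to the OPRAH trial (e.g. AEs occurring during intervention-related activities) reported spontaneously by the subject". Events that trial staff notice themselves fall under the same condition.

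The section on serious adverse events makes two exemptions. The first covers the hospital stay: "Our intervention starts after hospital discharge; therefore, all complications during hospitalization will not be reported as SAE". The second follows from the stated expectation that the intervention is low-risk: "all complications after discharge which are unmistakably caused by the surgery and/or medical treatment will not be reported as SAE". Where the relation to the intervention is in doubt, the case is discussed with the study surgeons, and it is reported if doubt remains.

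The Outcomes section lists adverse events as a secondary outcome. The adverse event row of Table 3 repeats the link rule and both exemptions, names medical records and self-report as sources, and gives T1 (discharge) to T6 as the time points.

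On when the intervention begins, the section on intervention description and procedures says "One week prior to planned surgery, patients receive the PAM and will receive access to and get instructions about the Atris app", and "During hospitalization, the treating physiotherapist and dietician guide the patients in the use of the app during their standard consultations".

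**The concern.** A harm outcome can be compared between randomised arms only if an event has the same chance of being counted in either arm. Here, counting depends on someone judging that the event may be linked to the trial, in a study where patients and therapists are not blinded. A difference in recorded events could then reflect the filter and not the intervention, and a real excess could be hidden if events are put down to surgery.

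This matters because the trial encourages activity soon after major cancer surgery. Readers will look to the adverse event table for reassurance, and it may reassure or alarm them for the wrong reason.

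The in-hospital exemption raises a separate issue. The reason given for it is a statement about timing that another section contradicts.

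**Working it through.** The plan states no figure on this point, so there is none to reproduce. The check compares sections and adds one illustration on assumed inputs.

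**1. Definition against recording.** The definition covers events "whether or not considered related to experimental intervention". The recording rule covers "All adverse events with a direct or possible link to the OPRAH trial". Events that meet the first and not the second are adverse events by definition but are not recorded. Because Table 3 repeats the rule in the outcome row, the filter shapes the outcome and not only expedited reporting.

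**2. Does the filter act equally by arm?**
- Randomization and blinding: neither patients nor therapists are blinded.
- Intervention description and procedures: intervention patients have three months of telephone and chat contact, in which events can be mentioned and linked.
- Usual care: there is no usual physiotherapy after discharge, and dietician contact varies by centre and type of surgery.
- Adverse events: the example of a linked event is one that occurs during intervention activities, which only one arm has.

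Both the chance of hearing of an event and the chance of calling it linked are therefore likely to be higher in the intervention arm.

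**3. What this does to the comparison.** Let the true risk p be the same in both arms, and let λ be the probability that an event is called linked and recorded. The recorded risk is p × λ, so the recorded risk ratio is λ(intervention) / λ(control), whatever p is. Assume λ = 0.02 in control and 0.10, 0.25 or 0.50 in the intervention arm; none of these values is in the documents. The recorded ratio is then 0.10/0.02 = 5, 0.25/0.02 = 12.5 or 0.50/0.02 = 25, against a true ratio of 1.

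With n = 67 per arm (the protocol's required number) and two-sided 0.05, the chance of a false significant difference was computed in two ways. The normal approximation is Φ[(d − 1.96·SE0)/SE1], with d the difference in recorded risks, SE0 from the pooled risk and SE1 from the separate risks. For 10% v 0.8%: d = 0.092, pooled risk 0.054, SE0 = √(2 × 0.054 × 0.946/67) = 0.0391, SE1 = √((0.09 + 0.0079)/67) = 0.0382, which gives Φ(0.40) = 0.66. Expected counts are small (67 × 0.004 = 0.27 in the lowest control cell), so the exact probability that Fisher's test gives p ≤ 0.05 is shown beside it.

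| True risk, both arms | Recorded, intervention v control | Normal approximation | Fisher, exact |
|---|---|---|---|
| 20% | 2% v 0.4% | 0.13 | 0.002 |
| 20% | 5% v 0.4% | 0.37 | 0.094 |
| 20% | 10% v 0.4% | 0.71 | 0.590 |
| 40% | 4% v 0.8% | 0.23 | 0.032 |
| 40% | 10% v 0.8% | 0.66 | 0.516 |
| 40% | 20% v 0.8% | 0.96 | 0.975 |
| 60% | 6% v 1.2% | 0.32 | 0.113 |
| 60% | 15% v 1.2% | 0.84 | 0.814 |
| 60% | 30% v 1.2% | 1.00 | 0.999 |

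The approximation overstates the problem where counts are lowest. Even so, the exact figure is above the nominal 0.05 in 7 of the 9 cases, and the recorded ratio is distorted in all of them. If λ were equal in both arms there would be no distortion; the bias depends entirely on λ differing.

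**4. When does the intervention start?**

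| Source | What it places before discharge |
|---|---|
| Serious adverse events | Nothing: the intervention is said to start after discharge |
| Intervention description and procedures | Device, app access and instruction one week before surgery; device worn day and night from at least 5 days before surgery; app guidance in hospital; activity and protein goals set as discharge approaches |
| Table 2 | No timing, but wearing the sensor, self-monitoring and goal setting are listed as intervention components |

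Randomisation follows the preoperative baseline, so the hospital stay falls after allocation. The stated reason for the in-hospital exemption does not agree with the schedule. Remote coaching does begin only after discharge.

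**The case against.** The strongest defence is that the rules lean towards recording: a possible link is enough, and an SAE of persisting doubt is reported. An exemption from SAE reporting also does not prove that an event goes uncollected, and the full protocol is not shown. The Statistical analysis section names no test of adverse events. All of this is fair, and it limits the point. It does not remove it, because the outcome row of Table 3 itself carries the filter and the exemptions, and a possible link is still a judgement made with the arm known.

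Four stronger readings are tempting, and the documents do not support them.
- **Harms cannot be compared at all.** Unplanned readmission within 30 days is a separate secondary outcome taken from medical records with no relatedness filter. Pain and fatigue are also unfiltered.
- **Control patients will have no recorded events, so a risk ratio is undefined.** The criterion is a link to the trial, and intervention activities are only an example. Controls also wear the taped-on thigh sensor, and the chair stand and step tests are outcome measures. A zero count is not shown.
- **Coaching begins before surgery.** Only the device, app and instruction do.
- **A given share of exposure has no capture.** Length of stay is not stated, the SAE exemption covers the hospital stay and not the preoperative week, and the general definition has no start at discharge.

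Timing also counts: the article appeared in November 2023, with recruitment due to end in December 2023, so new prospective collection could reach few patients.

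**Conclusion.** The point stands in limited form. As defined, the adverse event secondary outcome cannot give an unbiased comparison between arms, and the reason given for the in-hospital exemption conflicts with the protocol's own schedule.

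The conclusion rests on the stated rules, on unblinded patients and therapists, and on the inference that events are heard of and linked more often in the intervention arm. The size is unknown, and the illustrative ratios of 5 to 25 follow wholly from assumed linking probabilities. The usual direction would be against the intervention. Attribution to surgery could push the other way, so a null table would not be reassuring either.

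The primary outcome and its analysis are untouched. This should be corrected before harms are reported, but it does not threaten the main result.

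**What to change.** Separate the outcome from expedited reporting.

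- **Outcome.** Tabulate by arm all deaths, SAEs and complications from randomisation to T6. Take them in the same way in both arms from the medical records and self-report already named in Table 3.
- **Relatedness.** Record it as an attribute of each event, not as a condition for counting it.
- **Exemptions.** Limit the in-hospital and surgery-related exemptions to expedited reporting; exempted events still enter the table.
- **Patients already enrolled.** Use record review. Past self-reports came in unevenly by arm and cannot be repaired, so the record-based table should carry the comparison, with linked events listed separately as description.
- **Start of intervention.** Reconcile the section on serious adverse events with the section on intervention description and procedures, so that both give the same start.

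The cost is an amendment, a longer event form and more data entry from records that are already consulted for readmission and healthcare use. The table will also list many expected surgical complications. They should be similar in the two arms if the intervention has no effect on them, which is what the comparison is meant to show.

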### Outcomes

The primary outcome is recovery in physical functioning 6 months after hospital discharge and the most important secondary outcome is physical activity. Other secondary outcomes are lean body mass, pain, fatigue, muscle mass, protein and energy intake, physical performance, patient-specific activity limitations, self-efficacy, participation in social roles and activities, generic quality of life, global perceived effect, hospital readmission and adverse events. See Table 3 for a detailed description of the outcome measures with the corresponding follow-up time points.

**Table 3 Tab3:** Outcome measures

Construct	Measure	Abbrev	Description	Time points
***Primary outcome***				
Physical functioning	Computer Adaptive Testing (CAT) Dutch-Flemish Patient-Reported Outcome Measure Information System for Physical Functioning	CAT PROMIS-PF	The CAT PROMIS-PF is a digital questionnaire [37]. A CAT is a computer-administered measure in which a computer algorithm is used to select successive items based on responses to previous items. Using a 5-point Likert scale the questionnaire reflects the participant’ functioning in the past 7 days. The items cover a wide range of activities, from activities of daily living to more complex activities [38]. The CAT PROMIS-PF has sufficient psychometric properties in measuring the level of physical function of physiotherapy patients [39] and has been shown to be reliable and sensitive to change in surgical patients [40, 41].	T0, T2, T3, T4, T5, T6
***Most important secondary outcome***				
Physical activity	ActivPAL™		The ActivPAL (PAL Technologies Ltd., Glasgow, UK) is a thigh-worn tri-axial accelerometer and uses proprietary analysis algorithms to determine posture (sedentary time, upright time) and stepping (stepping time and steps). The Activpal will be affixed to the skin with hydrogel pads on the thigh. The ActivPAL is one of the most frequently used activity trackers in clinical research and has been shown to be a valid measure of posture and stepping [42–44]. Patients in both the intervention and control group will wear the ActivPAL for 5 days	T0, T1, T3, T5, T6
***Other secondary outcomes***				
Lean body mass	Bioelectrical Impedance Analysis	BIA	A single frequency bio electric impedance meter (50 kHz) will be used for the BIA. These impedance meters uses 4 electrodes to measures the impedance, resistance, reactance and phase angle. A BIA is a non-invasive validated method to assess body composition, fat-free mass (FFM) and appendicular skeletal muscle mass (ASSM) patients with cancer [45]. FFM is one of the factors the dietician uses to determine patients’ personal protein requirements. FFM will be measured with the formula of Kyle [46]	T0, T3, T5
Pain	Numeric Pain Rating Scale	NPRS	The NPRS is a measure of subjective intensity of pain in adult patients. The 11-point numeric scale ranges from ‘0’ (no pain) to ‘10’ (worst pain imaginable). The NPRS is a valid, reliable and usual tool to measure pain in postoperative patients [47, 48].	T0, T2, T3, T4, T5, T6
Fatigue	Dutch-Flemish Patient-Reported Outcome Measure Information System for Fatigue – Short Form	PROMIS F-SF	The PROMIS F-SF consists of seven items that measure both the experience of fatigue and the interference of fatigue on daily activities over the past week. The response scale is a 5-point Likert scale, ranging from 1 (never) to 5 (always). Total scores range from 7 to 35: a higher score indicating greater fatigue. The PROMIS F-SF showed acceptable reliability and validity and is suitable to measure fatigue across a diverse clinical population [49].	T0, T2, T3, T4, T5, T6
Muscle mass	Analyses of Computer Tomography	CT-analyses	CT images are routinely obtained in the oncological workup of lung and GI cancer patients, both pre- and postoperative. CT images obtained from whole-body PET/CT scans will be analyzed by a validated computer program AMUSE (acronym for Automatic MUscle and visceral/subcutaneous fat SEgmentor). The landmarks for the assessment of muscle mass will be the third lumbar vertebra (L3) and the fourth thoracic vertebra (Th4)	T0, T6
Protein and energy intake	48-h dietary recall		A 48-h dietary recall will be performed by trained interviewers, dietician researchers or graduate students, following a standard protocol. The intake of food items will be registered, including details of preparation methods, recipes, quantities and the size of portions, and the brands of products. The calculation of total energy intake and protein intake will be based on the database of ‘The Netherlands Nutrition Centre’. Protein intake will be calculated in gram per day. Energy intake will be calculated in kcal per day. Earlier studies suggested that a 48-h recall is superior to a single 24-h recall [50, 51].	T0, T2, T3, T5, T6
Physical performance	1) Hand grip strength 2) 30-s chair stand test 3) 2-min step test	1) - 2) 30SCST 3) TMST	1) Handgrip strength will be measured using the Jamar grip strength dynamometer as a measure of generalized muscle strength. The Jamar grip strength shows good reliability and can be used to measure changes in strength over time [52, 53]. The normative data of Dodds. et al. will be used as reference. [54] 2) The 30SCST will be used to measure functional lower extremity muscle functioning. The 30CST measures extremity strength in relation to demanding functional daily activities such as stair climbing [55]. The patient is seated in a chair and will be asked to complete as many full stands as possible in 30 s. The 30CST shows good reliability and criterion validity [56]. 3) The TMST will be used to measure exercise capacity [57]. The test requires the patients to march in place as fast as possible for 2 min while lifting the knees to a height midway between their patella and iliac crest when standing. Performance is defined as the number of steps completed in 2 min These performance tests are easy to perform at the patient’s home. The physical performance tests will be performed by trained (student) allied health professionals. Standard operating procedures will be used for all tests [58].	T0, T3, T5
Patient-specific activity limitations	Patient-specific Functional Scale	PSFS	The Dutch PSFS includes a list of 24 activities adapted from the activity list for patients with heart failure by Beurskens et al. and patients will be asked to indicate all activities that he or she was limited in performing within the previous week. [59] Patients have also the possibility to indicate any additional activities in the “other” section. The patient will be asked to prioritize their three most important activity limitations. Patients will then be asked to rate these activities on a numeric rating scale ranging from 0 to 10, where 0 indicates no limitations in performing the activity and 10 indicates that performing the activity is impossible. The PSFS is an appropriate measure for statistical comparisons in clinical research	T0, T2, T3, T4, T5, T6
Self-efficacy	General self-efficacy scale	GSES	The questionnaire contains 10 items with a 4-point response scale (1 = completely wrong, 4 = completely true). Total scores range from 10 to 40: a higher score indicating more self-efficacy. The GSES Is a valid tool to measure self-efficacy [60].	T0, T2, T3, T4, T5, T6
Participation in social roles and activities	CAT Dutch-Flemish Patient-Reported Outcome Measure Information System for participation	CAT PROMIS participation	The CAT PROMIS participation item bank including the item banks ‘Ability to participate in Social Roles and Activities’ and ‘Satisfaction with Social Roles and Activities’. The response scale is a 5-point Likert scale; a higher score indicates better participation. The CAT PROMIS item bank is a reliable and valid measurement of participation with limited administration time [61].	T0, T2, T3, T4, T5, T6
Generic Quality of Life	The 5-level EuroQol five-dimensional questionnaire	EQ-5D-5L	This EQ-5D-5L consists of five questions representing five health dimensions; mobility, self-care, usual activities, pain/discomfort and anxiety/depression. The EQ-5D-5L is added in order to carry out cost-effectiveness analysis. The EQ-5D-5L shows good psychometric properties and is suitable for economic evaluation studies in oncological patients [62].	T0, T2, T3, T4, T5, T6
Global perceived effect	Global Perceived Effect questionnaire	GPE	The Dutch version of the GPE will be used to measure the patient’s opinion of their recovery [63]. The questionnaire consists of two questions with a 7-point Likert scale. Patients will be asked to indicate to which extent they are recovered since the beginning of their recovery after surgery (1 = much better, 7 = much worse). In addition, patients will be asked how satisfied they are with their treatment since the beginning of their recovery after surgery (1 = very satisfied, 7 = very unsatisfied)	T0, T2, T3, T4, T5, T6
Hospital readmission	Medical Record Data		Unplanned *hospital readmissions* within 30 days after discharge will be reported	T3
Adverse event	Medical record data and self-reported		All adverse events with a direct or possible link to the OPRAH trial (e.g. AEs occurring during intervention-related activities) reported spontaneously by the subject or observed by the investigator or his staff will be recorded. This study will include patients undergoing oncological lung or GI surgery. These types of surgery are associated with a certain risk of postoperative complications. Our intervention starts after hospital discharge; therefore, all complications during hospitalization will not be reported as SAE. We expect that our, low-risk, post-discharge intervention will not have any negative influence on the occurrence complications after discharge. Therefore, all complications after discharge which are unmistakably caused by the surgery and/or medical treatment will not be reported as SAE. When there are doubts about the relation between the intervention and the occurrence of an SAE, these SAE’s will be discussed with the surgeons involved in this study	T1 t/m T6
